### Information and screening

Upon first contact, a researcher informs the possible participants briefly about the project and sends written information by mail or e-mail. If the candidate is still interested after having read the material, the staff member subsequently screens for exclusion criteria and invites the person to an information meeting after which participants give their written informed consent in accordance with Declaration of Helsinki II. The protocol has been approved by The Danish Regional Committees of the Capital Region on 4 July 2013 (number H-4-2013-070).

At the information meeting, a medical member of the research team delivers the information verbally followed by a health screening including blood pressure, blood samples, and heart auscultation to determine if the candidate can safely complete the interventions. Then, the participant performs a 30-second chair-stand test that we use for stratified randomization only.

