### Randomization

Following screening and health examinations, we enroll candidate participants and researchers who are not involved in interventions or tests that are sensitive to blinding randomize them using the open-source minimization program MinimPy 0.3 [58, 59]. To ensure even distribution of subjects throughout the study period, we decided to employ a stratified, biased coin minimization with 0.95 base probability and to use allocation ratios corresponding to the group sizes (see Statistics and power calculations section below). Participant stratification is based on a 30-second chair-stand test (<16 or ≥16) and on gender to ensure equal allocation to one of the five intervention groups and further to determine if the participant will participate in invasive acute mechanistic MPS trials (see Muscle protein synthesis section below), as demonstrated in Fig. 3.

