### Blinding

We achieve blinding by storing the randomization log file electronically without access for researchers performing the tests who could be affected by not being blinded. Specifically, blinded radiographers will perform magnetic resonance imaging (MRI) scans at the Department of Radiology, Bispebjerg-Frederiksberg Hospital, Copenhagen, Denmark. A blinded physiotherapist or physiologist will perform strength and functional assessments, and only one tester will assess each participant. Experienced staff not blinded to the intervention will perform dual-energy X-ray absorptiometry (DXA), muscle biopsies, anthropometry, and blood sampling. Blinded investigators will perform all analysis and interpretation of obtained data. We blind participants in supplementation-only groups, as the bags containing supplements are marked only by a code, and only relevant researchers can access the key file containing the explanation of the codes. For obvious reasons, we did not blind those performing exercises to intervention or supplement type, as stated in the study hypotheses.

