### Measurements

This section describes each measurement performed to evaluate the longitudinal effects of the chosen interventions. Table 3 displays the time points for each examination. At baseline, we test the peak isometric and isokinetic peak torques as well as leg extensor power in both legs to evaluate if a large side difference between thigh peak torques is associated with an improved or diminished response to the interventions.

**Table 3 Tab3:** Time schedule of participant engagement

Measurement	Enrollment	Baseline	6 months	12 months	18 months	Other
Enrollment						
Recruitment and screening	X					
Information and consent	X					
Primary outcome						
MRI CSA of quadriceps femoris		X	X	X	X	
Secondary outcomes						
Thigh isometric peak torque		X	X	X	X	
Thigh isokinetic peak torque		X	X	X	X	
Thigh power		X	X	X	X	
30-second chair-stand		X	X	X	X	
Muscle biopsy		X		X		
Body composition (DXA)		X	X	X	X	
Bone mineral density (DXA)		X		X		
Gut microbiome		X	X	X		
Fecal metabolome		X	X	X		
Plasma metabolome		X	X	X		
Acute muscle FSR		X		X		
Tertiary outcomes						
Blood samples		X	X	X	X	
Anthropometry		X	X	X	X	
Hand grip strength		X	X	X	X	
400-m gait speed		X	X	X	X	
SF-36 and PSQI		X		X		
Activity monitoring		X	X	X	X	
Registration of food consumption		X		X		At week 6
Sensory questionnaires			X	X		Weekly for 0–3 months
Satisfaction with Food-related Life scale		X	X	X		
Oral glucose tolerance test		X		X		
Qualitative interview		X			X	
Questionnaire on food habits		X				
Life story interviews						Ad hoc
Ethnographic fieldwork						Ad hoc

*Abbreviations: MRI CSA* magnetic resonance imaging cross-sectional area, *DXA* dual-energy X-ray absorptiometry, *FSR* fractional synthesis rate, *PSQI* Pittsburgh Sleep Quality Index, *SF-36* 36-item Short Form Health Survey

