##### 30-second chair-stand

The 30-second chair-stand test is a functional assessment of strength and endurance in the lower extremity by measuring the number of stands completed in 30 seconds with hands crossed on the chest [67]. The test is useful in characterizing the participant’s functionality and is also known to correlate with daily activity level [68].

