In a subset of participants from the five intervention groups, we will conduct experimental tracer studies before and after the 12-month intervention period to determine the extent to which the interventions affect the responsiveness of MPS to protein intake. The goal is to measure whether any of the interventions enhance the anabolic sensitivity to protein intake and thereby investigate if we can link the observed differences in muscle mass over the course of the intervention period to changes in the anabolic response to protein feeding. Thus, the outcome measure is the relative change in the FSR of muscle proteins from the basal condition, defined as the overnight fasted and resting state, to the average 4-h postprandial period after intake of a standard protein bolus. We are not aware of any data on changes in MPS responsiveness over time, and we therefore based the power calculations on a sum of our own published and unpublished data obtained in healthy elderly participants. We established the following parameters: expected average 4-h postprandial responsiveness to protein feeding from basal condition of 0.016 %/h (i.e., approximately corresponding to an increase in muscle protein FSR of 50 %) with an interparticipant SD on the increase of 0.017 %/h. We aim to be able to detect a 50 % change in responsiveness within a group over the course of the 12-month period (i.e., a change of 0.008 %/h in the increase in the muscle protein FSR from 0.016 %/h to 0.024 %/h). The SD for the change in responsiveness is set as 0.006 %/h. By including 10–12 participants, we obtain a power of at least 0.80 to detect a statistical difference over time within each intervention group. By taking the probability of dropouts into account, we decided to include 12 participants in the HRTW, LITW, and CARB groups and 15 in the WHEY and COLL groups, respectively.

Investigators will analyze data as intention-to-treat (except in subgroup analyses) as well as per protocol, and we will test the following groups against each other using one-way analysis of variance of the relative group changes from baseline to 12 months: (1) WHEY vs. COLL vs. CARB and (2) HRTW vs. LITW vs. WHEY. We will not conduct any interim analyses in this project.

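### The screening chair-stand count appears to go unused in the analysis of the chair-stand outcome, a modest loss of precision on one secondary outcome

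*Protocol article*

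**What the plan says.** Under Information and screening, the article ends the account of the information meeting with "Then, the participant performs a 30-second chair-stand test that we use for stratified randomization only". The Randomization section shows that use: "Participant stratification is based on a 30-second chair-stand test (<16 or ≥16) and on gender". Allocation follows screening, and the exclusion criteria in Table 1 contain no chair-stand threshold.

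Table 3 (Measurements) lists the chair-stand among the secondary outcomes, marked at baseline, 6, 12 and 18 months and not under Enrollment. The outcome is a count, obtained by "measuring the number of stands completed in 30 seconds with hands crossed on the chest".

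The Statistics and power calculations section tests WHEY vs. COLL vs. CARB and HRTW vs. LITW vs. WHEY "using one-way analysis of variance of the relative group changes from baseline to 12 months". It does not restrict this method to the primary outcome, and it names no covariate.

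No sentence says that there are two chair-stand tests before the intervention. That follows from reading the screening text beside Table 3: a test reserved for randomization is not also the outcome baseline.

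**The concern.** A single whole-number count has measurement error, and a change from that count carries the error into the outcome. In a relative change it also sits in the denominator. A second count of the same test, taken before allocation, would reduce the baseline part of this noise. The plan reduces that count to two classes for the minimization and then, as written, leaves it out of the analysis. The one-way ANOVA also ignores the minimization factor that the count defines.

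What is at stake is precision for one functional secondary outcome. The screening value precedes allocation, so entering it as a covariate does not bias the comparison of arms.

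**Working it through.** **Figures in the article.** None is given for the chair-stand: no SD, test-retest reliability, pre-post correlation or target difference. There is therefore no stated figure to reproduce. The only between-group power statement concerns quadriceps CSA and does not bear on this point.

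**Assumptions.** Scale the variance on one occasion to 1. Let r be the correlation of each pre-intervention count with the 12-month count, and r0 the correlation between the two pre-intervention counts. Both are assumed.

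**Formulas for residual variance.**
- Absolute change from one baseline: 2(1 − r)
- Absolute change from the mean of both counts: 1 + (1 + r0)/2 − 2r
- ANCOVA, one baseline: 1 − r²
- ANCOVA, both counts: 1 − 2r²/(1 + r0)

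**Example, r0 = r = 0.8.** Change 2 × 0.2 = 0.400. One-baseline ANCOVA 1 − 0.64 = 0.360. Two-count ANCOVA 1 − 1.28/1.8 = 0.289. Full change of method: 1 − 0.289/0.400 = 28%. Screening count alone: 1 − 0.289/0.360 = 20%.

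| r0 | r | Change | ANCOVA, one | ANCOVA, both | Saving, both vs. change | Saving, both vs. one |
|---|---|---|---|---|---|---|
| 0.7 | 0.7 | 0.600 | 0.510 | 0.424 | 29% | 17% |
| 0.8 | 0.8 | 0.400 | 0.360 | 0.289 | 28% | 20% |
| 0.9 | 0.9 | 0.200 | 0.190 | 0.147 | 26% | 22% |
| 0.8 | 0.7 | 0.600 | 0.510 | 0.456 | 24% | 11% |
| 0.9 | 0.8 | 0.400 | 0.360 | 0.326 | 18% | 9% |
| 0.9 | 0.7 | 0.600 | 0.510 | 0.484 | 19% | 5% |
| 0.95 | 0.9 | 0.200 | 0.190 | 0.169 | 15% | 11% |
| 0.95 | 0.8 | 0.400 | 0.360 | 0.344 | 14% | 5% |
| 0.95 | 0.7 | 0.600 | 0.510 | 0.497 | 17% | 2.5% |

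The first three rows assume equal correlations. The others let the two early tests agree more closely with each other than with a test 12 months later, which is the more plausible pattern.

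**If change from baseline is kept.** Averaging the two counts saves 25% at any r when correlations are equal, 17% at (r0, r) = (0.8, 0.7), 8% at (0.9, 0.7) and 4% at (0.95, 0.7).

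**Relative change.** The formulas above are for absolute change, whereas the plan uses relative change. A simulation with an assumed mean of 16 and SD of 4 gave a variance saving from averaging the two counts of about 29 to 34% with equal correlations of 0.7 to 0.9, and 12% at (0.9, 0.7).

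**The case against.** **The word 'only' may not concern the analysis.** The preceding sentence is about checking whether candidates can safely take part, so 'only' may mean that the chair-stand does not decide eligibility. That reading is fair, and a reader who infers an explicit ban on using the value goes further than the text. The point does not need a ban: the stated ANOVA uses one baseline and no covariate, so the screening count is unused on either reading.

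**Covariates for secondary outcomes usually belong in the analysis plan.** True, and silence would be no finding. But the article does not stay silent. It names an unadjusted method.

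**A reader might infer that about a fifth of the variance is lost.** The documents do not support that as a fact. It needs correlations of about 0.8, equal between all occasions, and the table shows how quickly the figure falls when they are unequal.

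**A reader might also infer a power gain from 59% to 72–74%.** Those figures arise with 30 per arm, equal correlations of 0.7 to 0.9 and a standardized difference of 80/140 = 0.57. That difference is the CSA assumption and has no link to chair-stand counts. The gain also merges two changes: at r = 0.7, one-baseline ANCOVA alone already gives 66%, and the screening count takes this to 74% with r0 = 0.7 but only 68% with r0 = 0.9 and 67% with r0 = 0.95.

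**The screening count may be unavailable or less comparable.** This stands. The article shows only the two-level class in use and does not say that the raw count is kept. For outcome assessments it states that "A blinded physiotherapist or physiologist will perform strength and functional assessments, and only one tester will assess each participant"; who tests at screening is not stated. The first attempt may also serve as familiarization. A practice effect common to all arms is absorbed if the screening count is a separate covariate, but poorer comparability would shrink the gain.

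**Conclusion.** The point holds as a modest efficiency gain. The article implies two chair-stand counts before the intervention and specifies an unadjusted analysis of relative change from one of them.

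Under the assumed pre-post correlations of 0.7 to 0.9, ANCOVA with both counts lowers residual variance by about 17 to 29% against an absolute change score in most combinations worked, and by 14 to 15% in the two with r0 = 0.95 and r of 0.8 or 0.9. Part of that comes from replacing change with ANCOVA. The share due to the screening count is about 2.5 to 22%, with the lower values applying when the two early tests agree more closely with each other than with the 12-month test. None of these figures can be fixed from the documents.

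The plan's analysis is not biased on this account, and the primary outcome, quadriceps CSA, is unaffected.

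**What to change.** 1. Under Information and screening, delete 'only', or replace it with a statement that the screening chair-stand is not used for eligibility.
2. In Statistics and power calculations, specify that the 12-month chair-stand count is analysed by ANCOVA with the baseline count and the screening count as separate continuous covariates. Do not average them, so that a practice effect is absorbed.
3. First confirm that the raw screening count was recorded. If only the class survives, enter the class (<16 or ≥16) as a factor; this still adjusts for the minimization factor, with a smaller gain.

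The cost is wording only, with no new measurement or visit. The Trial status section reports 153 of 205 randomized and 54 through the intervention, and no interim analysis is planned, so at the time of the article the change could still be specified before the data are analysed.

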### Randomization

Following screening and health examinations, we enroll candidate participants and researchers who are not involved in interventions or tests that are sensitive to blinding randomize them using the open-source minimization program MinimPy 0.3 [58, 59]. To ensure even distribution of subjects throughout the study period, we decided to employ a stratified, biased coin minimization with 0.95 base probability and to use allocation ratios corresponding to the group sizes (see Statistics and power calculations section below). Participant stratification is based on a 30-second chair-stand test (<16 or ≥16) and on gender to ensure equal allocation to one of the five intervention groups and further to determine if the participant will participate in invasive acute mechanistic MPS trials (see Muscle protein synthesis section below), as demonstrated in Fig. 3.

**Fig. 3 Fig3:**
[figure not shown]
Participant flow. N_total_ represents the expected number of inclusions in each group. N_acute_ represents the expected number of participants who will complete the measurements of fractional synthesis rate at 0 and 12 months. *COLL* Collagen supplementation, *CARB* Carbohydrate supplementation, *WHEY* Whey supplementation, *LITW* Light intensity resistance training and whey supplementation, *HRTW* Heavy resistance training and whey supplementation

### Interventions

The five intervention groups comprise the two arms of the study. One arm concerns the importance of supplementation using the three supplementation-only groups: carbohydrate supplementation (CARB; 20 g maltodextrin + 10 g sucrose), collagen supplementation (COLL; 20 g bovine collagen protein hydrolysate + 10 g sucrose), and whey supplementation (WHEY; 20 g whey protein hydrolysate + 10 g sucrose). All supplements were developed, prepared, and individually packaged by Arla Foods Ingredients Group P/S, Viby J, Denmark. The other arm investigates the importance of training loads and includes all groups supplemented with the aforementioned whey supplements, either without training (WHEY; the same group used in the supplementation arm), with light load home-based resistance training four times weekly (LITW), or with center-based heavy resistance training three times weekly (HRTW). Table 2 describes the training protocols in detail. All subjects consume the supplements twice daily, namely in the morning and at midday, preferably just before or during meals to increase satiety, thereby avoiding excess intake of calories. Participants who exercise are encouraged to take one supplement immediately after each training session. We conduct all interventions and tests at Bispebjerg Hospital. To report the improvement in thigh strength in repetition maximums (RM), we measure the thigh 3 RM in the knee extensor machine used for heavy resistance training (Super Executive Line; TechnoGym, Cesena, Italy) using as few attempts as possible every third month. To relate to the commonly used 1 RM, we will convert the result to a 1-RM equivalent using the Brzycki formula [60]: 1 RM = weight lifted × [36/(37 − repetitions)].

**Table 2 Tab2:** Exercise descriptions

Exercise regimen	LITW (three to five times weekly)	HRTW (three times weekly)
General comments	We instruct weekly in the first month and thereafter correct and instruct all exercises monthly, including one home visit. We increase the load accordingly when subjects can perform a given exercise correctly (i.e., optimal range of motion) and steadily (i.e., no shaking and maintaining a steady pace) as evaluated by the instructor. We use red, green, and blue TheraBand® rubber bands (Hygenic Corp., Akron, OH, USA). The weekly number of training sequences varies between three and five as follows: three, four, five, four, three, four, five, four, etc. (i.e., on average, four times weekly).	*Lower body exercises*: All exercises progress from 3 sets of 12 repetitions at 12 RM load to 5 sets of 6 repetitions at 6 RM load in 3-month cycles. The final 2 weeks of each cycle are tapering and testing periods with less intensive training. *Upper body exercises*: All exercises progress from 3 sets of 12 repetitions (12 RM) to 4 sets of 10 repetitions (10 RM).
Leg extension	Sitting on a chair and using rubber bands mounted around one leg of a chair and the relevant ankle, the participant extends and flexes the knee joint continuously and slowly. The exercise is performed three times for 1 minute each, separated by a break of similar duration, where they train the opposite leg. We ensured progress by decreasing the rubber band’s elasticity.	Super Executive Line (TechnoGym, Gambettola, Cesena, Italy). We separate sets by approximately 2 minutes. At all times, loading ensured training to fatigue. If participants could perform more repetitions after the final set, we added more weight at the next session.
Chair-stand/squat/leg press	Without using the arms, participants rise from and sit down on a chair continuously and slowly. They perform the exercise three times for 1.5 minutes separated by breaks of similar duration. We ensured progress by starting with the participant on a high chair, then converting to a low or no chair (i.e., squats).	Super Executive Line (TechnoGym, Gambettola, Cesena, Italy): as described for leg extension
Leg curl	Standing with rubber bands mounted around, for example, the leg of a chair and the participant’s ankle, the participant flexes and extends the knee joint continuously and slowly. The exercise is performed three times for 1 minute separated by breaks of similar duration, where they train the opposite leg. We ensured progress by decreasing the rubber band’s elasticity.	MED Line (TechnoGym, Gambettola, Cesena, Italy): as described for leg extension
Shoulder pull/pull-down	Using rubber bands mounted around, for example, a doorknob, the participant flexes and extends the elbow joint continuously and slowly while keeping elbows shoulder-wide. The participant performs the exercise three times for 1.5 minutes separated by a break of similar duration. We ensured progress by decreasing the rubber band’s elasticity.	TR Equipment model 9014 (Tranås, Sweden): We separated sets by a 2-minute break. At all times, loading ensured training to fatigue. If participants could perform more repetitions after the final set, we added more weight at the next session.
Arm stretch/push-up	Standing against a wall, the participant flexes and extends the elbow joints continuously and slowly. The exercise is performed three times for 1.5 minutes separated by breaks of similar duration. We ensured progress by increasing the distance to the wall, having the participant perform the exercise on the floor while supporting on hands and knees, or performing the exercise on the floor supporting on hands and feet.	TR Equipment model 9025 (Tranås, Sweden): as described for should pulldown

*RM* Repetition maximum

Participants monitor their adherence to protein supplementation and their home-based exercise in hard-copy diaries, whereas the trainers register the training adherence in the HRTW group. We stress the importance of registering only the actual number of supplements taken and exercises performed.

### Blinding

We achieve blinding by storing the randomization log file electronically without access for researchers performing the tests who could be affected by not being blinded. Specifically, blinded radiographers will perform magnetic resonance imaging (MRI) scans at the Department of Radiology, Bispebjerg-Frederiksberg Hospital, Copenhagen, Denmark. A blinded physiotherapist or physiologist will perform strength and functional assessments, and only one tester will assess each participant. Experienced staff not blinded to the intervention will perform dual-energy X-ray absorptiometry (DXA), muscle biopsies, anthropometry, and blood sampling. Blinded investigators will perform all analysis and interpretation of obtained data. We blind participants in supplementation-only groups, as the bags containing supplements are marked only by a code, and only relevant researchers can access the key file containing the explanation of the codes. For obvious reasons, we did not blind those performing exercises to intervention or supplement type, as stated in the study hypotheses.

### Measurements

This section describes each measurement performed to evaluate the longitudinal effects of the chosen interventions. Table 3 displays the time points for each examination. At baseline, we test the peak isometric and isokinetic peak torques as well as leg extensor power in both legs to evaluate if a large side difference between thigh peak torques is associated with an improved or diminished response to the interventions.

**Table 3 Tab3:** Time schedule of participant engagement

Measurement	Enrollment	Baseline	6 months	12 months	18 months	Other
Enrollment						
Recruitment and screening	X					
Information and consent	X					
Primary outcome						
MRI CSA of quadriceps femoris		X	X	X	X	
Secondary outcomes						
Thigh isometric peak torque		X	X	X	X	
Thigh isokinetic peak torque		X	X	X	X	
Thigh power		X	X	X	X	
30-second chair-stand		X	X	X	X	
Muscle biopsy		X		X		
Body composition (DXA)		X	X	X	X	
Bone mineral density (DXA)		X		X		
Gut microbiome		X	X	X		
Fecal metabolome		X	X	X		
Plasma metabolome		X	X	X		
Acute muscle FSR		X		X		
Tertiary outcomes						
Blood samples		X	X	X	X	
Anthropometry		X	X	X	X	
Hand grip strength		X	X	X	X	
400-m gait speed		X	X	X	X	
SF-36 and PSQI		X		X		
Activity monitoring		X	X	X	X	
Registration of food consumption		X		X		At week 6
Sensory questionnaires			X	X		Weekly for 0–3 months
Satisfaction with Food-related Life scale		X	X	X		
Oral glucose tolerance test		X		X		
Qualitative interview		X			X	
Questionnaire on food habits		X				
Life story interviews						Ad hoc
Ethnographic fieldwork						Ad hoc

*Abbreviations: MRI CSA* magnetic resonance imaging cross-sectional area, *DXA* dual-energy X-ray absorptiometry, *FSR* fractional synthesis rate, *PSQI* Pittsburgh Sleep Quality Index, *SF-36* 36-item Short Form Health Survey

